**Aim 2:** *Examine engagement of the hypothesized mechanisms at the 3- and 6-month f/u.* We hypothesize that those randomized to STEP, compared to ETAU, will have*:* **H2A:** higher attention to positive affect, assessed by implicit tasks; **H2B**: Increased gratitude and satisfaction with life, assessed by self-report; **H2C**: lower attention to negative affect, assessed by implicit tasks and self-report. Aim 2 analyses will use a repeated measures design and a multilevel or mixed effect modeling framework. For H2A, H2B, and H2C, the outcomes are continuous and a mixed effect general linear model will be used. Outcomes are repeatedly observed over follow-up and assessed at the scheduled follow-up (3M, 6M). For all hypotheses, we will treat the individual as the random effect. Treatment effects will be estimated as the weighted average of the differences between ETAU and STEP groups overall follow-up times, adjusting for follow-up time. ***Sample size and statistical power considerations***: As with H1, we determined minimal detectable effect sizes using Monte Carlo methods. This involved generating 1,001 simulated data sets representing our hypothesized effects, and our assumptions of a 10% loss by 3M and another 10% loss by 6M follow-up. We assumed repeated measures of the measures assessing the mechanisms (attention to positive affect, gratitude and satisfaction with life, and attention to negative affect) to have a stronger correlation within a respondent over time than the Aim 1 outcomes, and assumed *r* = .75, which results in a smaller effective sample size. Across the simulated data sets, we compute power as the proportion of replicates returning a significant effect in the hypothesized direction. Results of these models are summarized in Table 3, above. We summarize effects in terms of Cohen’s effect size statistics for clear expression of the minimum detectable effects. For Aim 2 outcomes, we will have sufficient power to detect small-to-medium effect sizes (*d* = .39).

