**Aim 3**: *Examine whether hypothesized mechanisms mediate reduction of suicidal events and ideation*. **H3:** Treatment-related changes in attention to positive affect, gratitude, satisfaction with life, and attention to negative affect at 3M follow-up will be related to improvements in SE and SI at the 6M f/u. Analysis: Mediation will occur when the outcomes (SE, SI) and the putative mediators (PA, gratitude and satisfaction with life, NA) are correlated, and that the distribution of the mediators varies according to treatment (Aim 2). We will approach the analysis using the Baron & Kenney (77) approach to mediation, with modifications for non-normal dependent variables, which is similar to the principal stratification approach to causal mediation analysis (78). We will approach this analysis using a cross-lagged panel model and a path analysis framework. Specifically, we will regress 6M outcomes and mediators on 3M outcomes and 3M mediators, and evaluate the effect of 6M outcomes regressed on 3M mediators accounting for any residual correlation of 6M outcome and 6M mediators and the 3M correlation of outcomes and mediators. All outcomes and mediators at all time points are regressed on treatment condition. We will quantify the total effect of treatment assignment in 6M outcomes, and the indirect effect of treatment in 6M outcomes via M3 mediators. Following Mandolando and Greenland (79), we will infer meaningful level of mediation if at least 10% of the total effect of treatment in 6M outcomes is mediated via M3 mediators. We will characterize the precision and statistical significance of mediation effects using bootstrap methods for interval estimation (80). ***Sample size and statistical power considerations.*** We used Monte Carlo methods to identify conditions in which a 10% difference (or greater difference) in the main treatment effect is to be detected when comparing to a model adjusting for the putative mediator. Finding a mediation effect requires that the treatment group have a different distribution on the putative mediator (attention to positive affect, gratitude and satisfaction with life, attention to negative affect) and the mediator be related to the outcomes (SE, active SI). In plausible scenarios (a unit standard deviation difference on the mediator across treatment group), and a (polyserial) correlation of 0.3 or greater between the mediator and the outcome, we will have adequate (at least 88%) power to detect a 10% mediated effect of treatment group and the outcome (n = 162, 81 per group). Similarly, if the treatment produces a net half standard deviation difference in the mediator (reflecting a clinically meaningful change), and the mediator has a (polyserial) correlation of at least .25 with the outcome, we will have 83% power to detect the target mediated effect.

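### Aim 3 infers mediation from a 10% share with no interval or test made a condition, and its stated 83% power fits only that rule

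*Protocol*

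**What the plan says.** Aim 3 fits a cross-lagged path model: "we will regress 6M outcomes and mediators on 3M outcomes and 3M mediators", with every variable also regressed on treatment. The decision rule is: "we will infer meaningful level of mediation if at least 10% of the total effect of treatment in 6M outcomes is mediated via M3 mediators". The sentence after it reads: "We will characterize the precision and statistical significance of mediation effects using bootstrap methods for interval estimation". It does not say that the interval decides anything.

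The power paragraph used simulation to "identify conditions in which a 10% difference (or greater difference) in the main treatment effect is to be detected when comparing to a model" that adjusts for the mediator. It adds that "Finding a mediation effect requires that the treatment group have a different distribution on the putative mediator", without naming a test or an alpha for that requirement. Two scenarios are given for "n = 162, 81 per group":
- "a unit standard deviation difference on the mediator across treatment group" with a polyserial correlation of at least .30: power at least 88%.
- A half-SD difference with a correlation of at least .25: power 83%.

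No total treatment effect and no false-positive rate are given for Aim 3. The opening of the same section rules out multiplicity adjustment.

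**The concern.** The share mediated is a ratio of two noisy estimates, and the plan compares its point estimate with a fixed cut. At this sample size the arms can differ on a mediator by chance. If that mediator is also related to the outcome, the chance difference passes straight into an apparent indirect effect. As written, mediation could be inferred while the bootstrap interval for the indirect effect covers zero, and the plan does not say which of the two governs. The power text answers how often the cut is reached, which is easier than showing an indirect effect. At stake is the claim that STEP works through positive and negative affect.

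**Working it through.** **Inputs.** From Aim 3: 81 per arm, correlations .30 and .25, mediator shifts 1 and 0.5 SD, stated power at least 88% and 83%. The total effect is not stated for Aim 3, so I assume a range from elsewhere in the protocol:
- Suicidal events: 38% vs 17% (Aim 1D) and 38% vs 19% (pilot).
- Active ideation: 50% vs 32% (pilot) and 50% vs 34.8% (the H1B detectable effect of .31, taking 50% in the control arm).

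**Simulation.** 3,000 replicates per setting. The mediator has unit SD within arm. The binary outcome comes from a latent normal variable with the stated correlation within arm. The share is ab/(ab + c'), where a is the treatment-to-mediator effect, b the mediator-outcome effect and c' the direct effect. A 95% Monte Carlo interval for ab stands in for the bootstrap. The 3-month outcome is not in the model.

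**Step 1: the stated power.**

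| Total effect | 1 SD, r=.30: 10% rule | plus interval | 0.5 SD, r=.25: 10% rule | plus interval |
|---|---|---|---|---|
| 38 vs 17 | 98-99% | about 80% | 80-82% | about 55% |
| 38 vs 19 | 98-99% | 80-82% | about 85% | 54-57% |
| 50 vs 32 | 99% | 85% | 89% | 59-61% |
| 50 vs 34.8 | 98% | 85% | 90% | 59-62% |

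The 10% rule is consistent with at least 88% and brackets 83%. Exact reproduction is not possible, because the total effect and the definition of the correlation are not stated.

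A hand check shows why 83% cannot come from a significance rule, taking both paths at two-sided 5% with r = .25 and 38% vs 17%:
- Treatment to mediator: SE = sqrt(2/81) = 0.157. Power = Phi(0.5/0.157 - 1.96) = Phi(1.22) = 0.89.
- Mediator to outcome: pooled event rate 27.5%, so the observed correlation is .25 x phi(z)/sqrt(p(1-p)) = .25 x 0.747 = .187. Then atanh(.187) x sqrt(159) = 2.38, and power = Phi(0.42) = 0.66.
- Product: 0.89 x 0.66 = 0.59.

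At 50% vs 32% the same steps give 0.89 x 0.71 = 0.63. The mediator-outcome path alone stays below 83%, however far STEP moves the mediator.

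**Step 2: declarations by chance.** Suppose STEP does not move the mediator, so a has mean 0 and SE 0.157. On the latent scale the total effect is c = z(p1) - z(p2) and b is about r. The share reaches 10% when a >= 0.1c/r, so P is about 1 - Phi(0.1c/(0.157r)). Example, 38% vs 17% and r = .30: c = -0.305 + 0.954 = 0.649; 0.0649/.30 = 0.216; 0.216/0.157 = 1.38; P = 8.4%.

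| Total effect | c | r=.25: formula / simulated | r=.30: formula / simulated |
|---|---|---|---|
| 38 vs 17 | 0.649 | 4.9% / 6% | 8.4% / 9% |
| 38 vs 19 | 0.572 | 7.3% / 8% | 11.2% / 11% |
| 50 vs 32 | 0.468 | 11.7% / 12% | 16.1% / 16-17% |
| 50 vs 34.8 | 0.391 | 16.0% / 15% | 20.4% / 20% |

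By simulation, about half the suicidal-event effect gives 22-27%, and no total effect gives 38-42%. Adding the interval condition brings these settings to about 1-3%.

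**Step 3: several mediators.** Aim 3 names four constructs and two outcomes. If four mediators were independent, the chance of at least one false claim for suicidal events would run from 1 - 0.94^4 = 22% to 1 - 0.89^4 = 37%. The constructs are unlikely to be independent, so this is an illustration.

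**The case against.** The plan does not ignore uncertainty. It promises bootstrap intervals and statistical significance, names a Baron-Kenny approach, and says mediation needs a mediator that differs by arm. The 10% figure can be read as a size threshold beside a test. If the arm difference had to reach p < .05, false declarations would fall to about 2-3%. This stands as a charitable reading, and it means the fault is a rule that does not say what binds, not a total absence of error control. It does not dispose of the point, because the stated 83% belongs to the rule without significance.

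Four stronger readings are tempting and are not supported:
- **A false-claim rate of 15-35% at this sample size.** A continuous-outcome model with r = .30 and no 3-month outcome gives 35%, 21% and 15% at total effects of .2, .35 and .46. Aim 3 regresses on the 3-month outcome. Adding it (correlation .5 over time, as in the Aim 1 power text, and an assumed .3 with the mediator) gives 23%, 10% and 5%. Binary outcomes give the rates in Step 2.
- **Mediator shifts that contradict Aim 2.** Aim 2 says "For Aim 2 outcomes, we will have sufficient power to detect small-to-medium effect sizes" (d = .39). A minimum detectable effect is a floor, and the Aim 3 scenarios are conditional, so 1 and 0.5 SD contradict nothing.
- **A model invalid without baseline terms.** The 3-month outcome absorbs part of baseline severity, and the protocol does not exclude baseline covariates. Adding them is an improvement only.
- **A trivial power cost.** With a continuous outcome, 83% would fall only to about 79%. The polyserial correlations point to categorical outcomes, for which the fall is much larger. The milder figure could apply only if ideation is analysed as a proportion of weeks.

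**Conclusion.** The point holds in a limited form. The protocol states an inference rule with no uncertainty condition, and its stated 83% is reachable, in every setting run, only under that rule. Chance declarations per mediator are roughly 6-11% for suicidal events and 12-20% for active ideation, rising to about 40% when STEP has no total effect; control is worst where the treatment works least.

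These rates assume binary outcomes, r = .25-.30, a share counted in the protective direction only, and no 3-month outcome in the model. They depend on how the share is computed: as a change in the logistic coefficient they are 2-4% for suicidal events and 7-11% for ideation; counting a 10% share in either direction they are 15-26% and 28-41%. Aim 3 is labelled tertiary/exploratory, so no primary or secondary endpoint is touched.

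**What to change.** State that mediation is inferred only if the bootstrap 95% interval for the indirect effect excludes zero. The 10% share may stay as an additional size threshold. Define how the share is computed, and report it with its own interval.

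Restate power for the combined rule with binary outcomes, giving the assumed total effect and saying whether the correlation is within arm or pooled. On the assumptions above it is about 79-85% for 1 SD and r = .30, and about 54-62% for 0.5 SD and r = .25. Optionally, add the baseline mediator and baseline outcome, both already collected, to the paths.

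The cost is a few sentences and a re-run of an existing simulation. No new data are needed. The real price is that the stated power falls materially in the half-SD scenario.

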
# SUPPORTING DOCUMENTATION AND OPERATIONAL CONSIDERATIONS

## Regulatory, Ethical, and Study Oversight Considerations

### Informed Consent Process

#### Consent/assent and Other Informational Documents Provided to participants

Consent and assent forms describing in detail the study intervention, study procedures, and risks will be given to the participant and (if under 18) their guardian. If a participant turns 18 during the course of the study, they will be re-consented with the Consent Form. Stakeholder consents contain this same information and written documentation of informed consent will be completed prior to starting the study intervention for both participants and stakeholders. The following consent materials are submitted with this protocol:

- Consent form for participant (age 18)
- Parent permission form for participant (under age 18)
- Assent form
- Consent form for parent
- Consent form for Stakeholders, who include clinicians, administrators

#### Consent Procedures and Documentation

Our team has developed effective procedures for recruiting; study research assistants will screen for eligibility through review of admission notes to identify participants hospitalized due to suicide risk. They will then obtain approval from clinical staff at Butler Hospital, Bradley Hospital, and the BCH to approach the participant to ascertain interest and confirm that the patient does not have psychotic thoughts and has the cognitive capacity to understand the study. If interested, research staff will obtain informed parent consent as well as adolescent assent and schedule a baseline assessment to be conducted on the unit, which will include confirmation of suicide risk with the C-SSRS. Additionally, if adolescents are interested in participating in the study, but parents are not, adolescents will be allowed to participate with their parent’s consent.

Parents who are interested in the study will be contacted to set up a consenting call to allow ample time to explain study details and answer any questions. Prior to the consenting call, the RA will create a record ID in REDCap and electronically send a link to the appropriate consent documents to the parent/guardian. The RA will also confirm receipt of this link. At the time of the call, the RA will ask the parent to open the REDCap link and will guide them through the consent form and answer questions as they arise. The REDCap consent documents have been set to include “required responses” in all sections where participants must opt in or out of audio recording, different avenues of contact, and the NIMH NDA, as well as provide their initials to confirm these choices before they can move onto the next section. This is done to minimize the possibility of completing the forms partially or incorrectly. The RA will guide the parent on where to sign and date the document before submitting. Once the consent document is completed, the RA will review the consent form for completion or errors. If any mistakes are found, the RA will prompt the parent to revise those errors by returning to the consent document using the same link. Once the consent process is finalized, a second research team member will review the consent form to verify that it was completed correctly before the study commences with the participant. The secondary check will be noted in our internal tracking log.

For adolescent assent, the RA will meet with the teen in-person on the unit to complete the electronic assent form. The procedures for information verification and secondary quality assurance checks are the same as above.

If a parent is not fluent in English but they are fluent in Spanish, we will have Spanish consent forms and obtain consent with a native Spanish speaker, typically an RA, or utilize translator services at each respective hospital, if necessary, in order to obtain informed consent. We will use Spanish language versions of self-report forms where available, and translate those that are not available in Spanish.

### Study Discontinuation and Closure

This study may be temporarily suspended or prematurely terminated if there is sufficient reasonable cause. Written notification, documenting the reason for study suspension or termination, will be provided by the suspending or terminating party to study participants, investigator, funding agency, and regulatory authorities. If the study is prematurely terminated or suspended, the MPIs will promptly inform study participants, the Institutional Review Board (IRB), DSMB, and sponsor/funding agency and will provide the reason(s) for the termination or suspension. Study participants will be contacted, as applicable, and be informed of changes to study visit schedule.

Circumstances that may warrant termination or suspension include, but are not limited to:

- Determination of unexpected, significant, or unacceptable risk to participants
- Insufficient compliance to protocol requirements
- Data that are not sufficiently complete and/or evaluable
- Determination of futility

The study may resume once concerns about safety, protocol compliance, and data quality are addressed, and satisfy the funding agency, sponsor, IRB, and other relevant regulatory or oversight bodies (Safety Officer, DSMB).

### Confidentiality and Privacy

Participant confidentiality and privacy is strictly held in trust by the participating investigators, their staff, the safety and oversight monitor(s), and the sponsor(s) and funding agency. This confidentiality is extended to the data being collected as part of this study. Data that could be used to identify a specific study participant will be held in strict confidence within the research team. No personally-identifiable information from the study will be released to any unauthorized third party without prior written approval of the sponsor/funding agency.

Limits of confidentiality are restricted to concerns about safety to self and others. Parents will not have access to their child’s messages, and none of the messages are intended to assess safety risk. Reports of abuse or neglect will be investigated further. Should a participant disclose abuse, neglect, intent to harm someone else, etc., a hotline call and report will be made to the appropriate child and family agency within 24 hours.

All research activities will be conducted in as private a setting as possible.

The Safety Officer [name], other authorized representatives of the sponsor or funding agency, representatives of the Institutional Review Board (IRB), regulatory agencies, may inspect all documents and records required to be maintained by the investigator, including but not limited to, medical records for the participants in this study. The clinical study site will permit access to such records.

The study participant’s contact information will be securely stored at each clinical site for internal use during the study. At the end of the study, all records will continue to be kept in a secure location for as long a period as dictated by the reviewing IRB, Institutional policies, or sponsor/funding agency requirements.

Study participant research data, which is for purposes of statistical analysis and scientific reporting, will be transmitted to and stored at the Data Coordinating Site, based in the Lifespan Healthcare System and Brown University. This will not include the participant’s contact or identifying information. Rather, individual participants and their research data will be identified by a unique study identification number. The study data entry and study management systems used by clinical sites and by data coordinating site research staff will be secured and password protected. At the end of the study, all study databases will be de-identified and archived at the data coordinating center.

Measures Taken to Ensure Confidentiality of Data Shared per the NIH Data Sharing Policies

It is NIH policy that the results and accomplishments of the activities that it funds should be made available to the public (see <https://grants.nih.gov/policy/sharing.htm>). The PI will ensure all mechanisms used to share data will include proper plans and safeguards for the protection of privacy, confidentiality, and security for data dissemination and reuse (e.g., all data will be thoroughly de-identified and will not be traceable to a specific study participant). Plans for archiving and long-term preservation of the data will be implemented, as appropriate.

**Certificate of Confidentiality**

To further protect the privacy of study participants, the Secretary, Health and Human Services (HHS), has issued a Certificate of Confidentiality (CoC) to all researchers engaged in biomedical, behavioral, clinical or other human subjects research funded wholly or in part by the federal government.  Recipients of NIH funding for human subjects research are required to protect identifiable research information from forced disclosure per the terms of the NIH Policy (see <https://humansubjects.nih.gov/coc/index>). As set forth in [45 CFR Part 75.303(a)](https://www.ecfr.gov/cgi-bin/text-idx?SID=f3e9328bbbd5aabe8e639ca48dcbcc7f&mc=true&node=se45.1.75_1303&rgn=div8) and [NIHGPS Chapter 8.3](https://grants.nih.gov/grants/policy/nihgps/HTML5/section_8/8.3_management_systems_and_procedures.htm), recipients conducting NIH-supported research covered by this Policy are required to establish and maintain effective internal controls (e.g., policies and procedures) that provide reasonable assurance that the award is managed in compliance with Federal statutes, regulations, and the terms and conditions of award. It is the NIH policy that investigators and others who have access to research records will not disclose identifying information except when the participant consents or in certain instances when federal, state, or local law or regulation requires disclosure. NIH expects investigators to inform research participants of the protections and the limits to protections provided by a Certificate issued by this Policy.

### Future Use of Stored Specimens and Data

Data collected for this study will be analyzed and stored at the Brown University. The de-identified, archived data will be transmitted to the NIMH National Data Archive (NDA), on a schedule dictated by the NDA, for use by other researchers outside of the study. Permission to transmit data to the NIMH NDA will be included in the informed consent.

When the study is completed, access to study data and/or samples will be provided through the NIMH NDA.

